### Sample size calculation, statistical considerations, and trial feasibility

The sample size is based on a superiority design assuming a response rate to ferric carboxymaltose of 75% (per primary endpoint definition) by week 12. A response rate of 60% is assumed in the control group. This results in a 15% advantage for the treatment group which is considered medically meaningful. In order to achieve a statistically significant result with 90% power at a significance level of α = 0.05, 400 patients are required to be randomized according to the Pocock formula
[19]:

$$n=f\left(\alpha ,\beta \right)\times \left[p1\times \left(100-p1\right)+p2\times \left(100-p2\right)\right]/{\left(p2-p1\right)}^{2}$$

where p1 and p2 are the response rates in the control and experimental groups, respectively, and f(α, β) = [*Φ*^- 1^(α/2) + *Φ*^- 1^(β)]^2^.

To account for potential patient drop-outs over the 12-week study period, the sample size is estimated at 450 patients (225 per group). Although this number appears to be rather high, recruitment should be accomplished within several months. Each of the six participating centers treats at least 500 patients for gastric cancer every year which sums up to a volume of 3,000 patients per year. Based on the assumption of an incidence rate of 15% for postoperative anemia (18% in the sponsor’s institution) 400 patients may be recruited within one year.

The outcome parameters will be analyzed by a Pearson chi-square test or Fisher’s exact test (patient age and gender, clinicopathologic data, and morbidity) and Student’s t-test (Hb-level before treatment and hospital days after treatment). The Z-test will be used to determine whether or not a significant difference exists between two groups during follow-up.

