## Methods

### Study population, inclusion, and exclusion criteria

All patients with a hemoglobin-level ≥ 7 g/dl to <10 g/dl at postoperative days 5 to 7 after oncologic gastrectomy for gastric cancer will be eligible for screening. All patients aged 20 years and over and willing to give informed consent will be eligible. Participation in another trial interfering with the outcome of this study, language problems, lack of compliance, mental inability, unstable angina or myocardial infarction within 6 months of the trial, severe respiratory disease, ASA (American Society of Anesthesiologists) Score >3, inadequate liver, kidney, and bone-marrow functions (evaluated by measurement of white blood cell count (WBC), platelets, aspartate aminotransferase (AST), alanine aminotransferase (ALT), C-reactive protein (CRP), and creatinine), pregnancy/lactation, and Eastern Cooperative Oncology Group (ECOG) status >1 will be considered unspecific exclusion criteria. Further, patients with a known history of hypersensitivity or allergy to ferric carboxymaltose, active inflammatory disease (surgical, site infection, pneumonia, Systemic Inflammatory Response Syndrome (SIRS)), history of previous erythropoietin or iv-iron administration within 4 weeks prior to screening, history of iron overload (hemochromatosis) and anemia due to reasons other than iron deficiency will not be eligible for this trial. The study protocol was approved by the Institutional Review Board (IRB) of the National Cancer Center Korea on 7 November 2012 (NCCCTS-12-644). All participating centers approved the trial by their local IRBs subsequently. Further, the trial was registered in the clinical trials database (NCT01725789) (Figure 
1).

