### Procedures

#### General procedures

After consenting to participate in the trial, patients will be randomized to either one of the two treatment groups (500 to 1,000 mg ferric carboxymaltose (Ferinject®) *vs.* placebo (0.9% saline)). After inclusion of eligible patients medical history will be taken and all concomitant diseases and medications will be recorded. All trial participants will receive routine examination and blood testing for the following parameters: hemoglobin, RBC, WBC, platelets, serum ferritin, transferrin saturation, AST, ALT, CRP, and creatinine.

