#### Follow-up

Follow-up visits will take place at 3 and 12 weeks (±7 days) after the study intervention. On the follow-up visits patients will undergo blood testing and QoL evaluation as described above.

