### Study objectives

#### Primary endpoint

The primary efficacy endpoint will be the number of responders defined as an increase of the hemoglobin level of at least 2 g/dl related to the baseline hemoglobin measured after randomization at 12 weeks after administration of either placebo or ferric carboxymaltose.

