#### Secondary endpoints

Major secondary endpoints will be: percentage of patients with Hb ≥10, 11, and 12 g/dL at 3 and 12 weeks (independent of alternative anemia management including transfusion or use of erythropoietin stimulating agents), percentage of patients requiring alternative anemia management therapy, average time-to-response (Hb increase ≥2 g/dL and/or Hb ≥10 g/dL) (independent of alternative anemia management including transfusion or use of erythropoietin stimulating agent, development of Hb, ferritin, and transferrin saturation over the study duration (12 weeks) independent of alternative anemia management including transfusion or use of erythropoietin stimulating agents and finally safety/tolerability of ferric carboxymaltose. QoL as one of the most important secondary endpoints will be assessed by EORTC QLQ C-30 and STO-22 questionnaires at 3 and 12 weeks.

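### The only method named for comparing the arms during follow-up is an unspecified two-group Z-test; if it is used for Hb, ferritin and transferrin saturation, it gives up precision that baseline adjustment would recover at no cost

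*Protocol article*

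**What the plan says.** The statistical paragraph (Protocol article, Sample size calculation, statistical considerations, and trial feasibility) names three kinds of test.

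- Chi-square or Fisher's exact test, for demographic, clinicopathological and morbidity variables.
- A t-test with a short list of its own: "Student’s t-test (Hb-level before treatment and hospital days after treatment").
- For everything after treatment, one sentence: "The Z-test will be used to determine whether or not a significant difference exists between two groups during follow-up". No variable, scale, visit or covariate is attached to it.

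The section Secondary endpoints contains both kinds of outcome that a Z-test could serve. One is binary: "percentage of patients with Hb ≥10, 11, and 12 g/dL at 3 and 12 weeks". The other is continuous: "development of Hb, ferritin, and transferrin saturation over the study duration (12 weeks").

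The same markers are available before treatment. General procedures lists the blood test done for all participants: "hemoglobin, RBC, WBC, platelets, serum ferritin, transferrin saturation, AST, ALT, CRP, and creatinine". Under Follow-up the blood tests are repeated: "Follow-up visits will take place at 3 and 12 weeks (±7 days) after the study intervention". Methods against bias states that randomisation is stratified by center (six) and by need for adjuvant chemotherapy.

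**The concern.** How three laboratory markers develop over 12 weeks is a longitudinal question about continuous variables with a known starting value. The one method named for follow-up has no place for that starting value, for visit, or for the factors used to stratify randomisation. Neither of the other named tests fills the gap: the t-test is confined to pre-treatment Hb and length of stay, and the chi-square and Fisher tests are assigned to categorical characteristics and morbidity.

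What is at stake is precision on secondary endpoints. If the Z-test is used for the markers, their confidence intervals are wider than the collected data require. The sentence is also too open to tell a reader which analysis will be run.

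**Working it through.** **1. The plan's own figure.** With the formula in the sample size section, response rates of 60% and 75%, 90% power and α = 0.05 (two-sided through α/2):

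n per arm = (1.960 + 1.282)² × [60×40 + 75×25] / 15² = 10.507 × 4275 / 225 = 199.6, so 200 per arm and 400 in total.

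The stated 400 is reproduced. It concerns the binary responder endpoint and does not depend on how the markers are analysed.

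**2. Inputs for the markers.** From the plan: 1:1 allocation and 200 patients per arm before the drop-out allowance. Not in the plan: the correlation r between baseline and follow-up values. I assume r = 0.3, 0.5 and 0.6, the same in both arms.

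**3. Formulas.** Take the variance of a plain comparison of follow-up values as 1.

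- ANCOVA: 1 − r².
- Comparison of changes: 2(1 − r), if the baseline and follow-up SDs are equal.
- Unadjusted completers needed to match ANCOVA on 400: 400 / (1 − r²).
- Power: take an effect that has 80% power without adjustment at 200 per arm, that is (1.960 + 0.842) × √(2/200) = 0.280 SD. With variance factor v, power is Φ(2.802/√v − 1.960).

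**4. Results.**

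| r (assumed) | ANCOVA factor | Change factor | Unadjusted N matching ANCOVA on 400 | Power, follow-up values | Power, changes | Power, ANCOVA |
|---|---|---|---|---|---|---|
| 0.3 | 0.91 | 1.40 | 440 | 80% | 65.8% | 83.6% |
| 0.5 | 0.75 | 1.00 | 533 | 80% | 80.0% | 89.9% |
| 0.6 | 0.64 | 0.80 | 625 | 80% | 87.9% | 93.8% |

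**5. Unequal SDs.** Let k be the baseline SD divided by the follow-up SD. The change factor is then 1 + k² − 2rk. Subtracting the ANCOVA factor leaves (k − r)², which is never negative. So ANCOVA is at least as precise as a test on changes whatever k is; only the size of the gap in the table depends on equal SDs.

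**6. Where Hb is likely to lie.** Entry is limited: "All patients with a hemoglobin-level ≥ 7 g/dl to <10 g/dl at postoperative days 5 to 7". A narrow range of starting values tends to lower r, so the row for r = 0.3 (a 9% reduction in variance) may be the relevant one for Hb. Ferritin and transferrin saturation have no such entry limits, but the document gives no r for them either.

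**7. Chance imbalance.** With 200 per arm, the standard error of the baseline difference is √(2/200) = 0.10 SD, so in 95% of trials it lies within ±1.96 × 0.10 = ±0.20 SD. If baseline Hb were spread evenly over 7 to 10 g/dl (an assumption), the SD would be 3/√12 = 0.87 g/dl and the range about ±0.17 g/dl. This is random error that the unadjusted standard error already covers; adjustment removes the part that baseline predicts.

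**The case against.** The strongest reply is that the sentence on the Z-test never mentions Hb, ferritin or transferrin saturation. A Z-test for proportions is an equally natural reading: the sample size in the same section compares two response rates, and the secondary endpoints include several Hb-threshold percentages. This stands, and is why the point is conditional.

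Three further inferences are tempting and not supported.

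- A reader might conclude that baseline is ignored. The document does not say so. A Z-test on changes would use it, and the primary endpoint is itself defined from baseline: "increase of the hemoglobin level of at least 2 g/dl related to the baseline hemoglobin measured after randomization".
- A reader might conclude that each visit is tested separately and that the week-3 value of a patient who misses week 12 is lost. The text says neither.
- A reader might take the t-test on pre-treatment Hb as a substitute for adjustment. It is not presented as one and alters no treatment estimate.

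The validity argument also stands. An unadjusted comparison in a randomised trial has no systematic bias from chance imbalance and does not inflate the type I error.

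It can also be said that covariates and model structure belong in an analysis plan that is not shown here. That is right for what the article leaves out, and no omission is held against it. But the article does name a method for follow-up, and that method can be judged as written: it is open about its target and, on either continuous reading, not the most precise use of the data.

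**Conclusion.** The point holds as a free improvement on secondary endpoints. The article fixes an unspecified Z-test as its only between-group method for follow-up. Applied to the three markers, as follow-up values or as changes, that test would be valid but less precise than a baseline-adjusted analysis of data already collected. Against follow-up values the variance falls by 9%, 25% or 36% at r = 0.3, 0.5 or 0.6.

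The size rests on assumed correlations common to both arms, and for Hb it may be close to the smallest of these figures. It also depends on the Z-test being meant for these markers, which the text leaves open. Nothing here touches the primary responder endpoint or the sample size of 400, raised to 450 for drop-out.

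**What to change.** State which variables the Z-test covers, and limit it to proportions.

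For Hb, ferritin (log scale) and transferrin saturation, specify ANCOVA at each visit or, preferably, one repeated-measures model over weeks 3 and 12 with treatment, visit, treatment-by-visit, the baseline value of the marker, center and adjuvant-chemotherapy stratum. Report adjusted differences between the arms with 95% confidence intervals at weeks 3 and 12; for ferritin, back-transform them to ratios. The repeated-measures form also uses the week-3 value of a patient without a week-12 value. This is relevant because the step from 400 to 450 implies an allowance for loss of about 11% (1 − 400/450).

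The cost is a change of wording in the analysis section or the analysis plan, made before unblinded data are seen. It needs no new measurements, visits or patients.

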### Safety

Stopping rules of the study medication will not apply due to a single administration of ferric carboxymaltose. However, in case of hypersensitivity or anaphylactic reactions immediate interruption of infusion will be mandatory. Further management will be left to the discretion of the physician on duty. Any (serious) adverse event ((S) AE), any (unexpected) (serious) adverse drug reaction, and any suspected unexpected serious adverse reaction (SUSAR) will be documented. All SAEs, SADs, and SUSARs will have to be documented and reported to the IRB by the responsible investigator according to local regulations.

### Documentation and data handling

All information required by the study protocol and collected during this trial will be entered in the electronic case report form (eCRF) using the web-based eVelos system (http://eresearch.ncc.re.kr/eres/jsp/ereslogin.jsp). The completed eCRFs will be reviewed and signed by the investigator or subinvestigator and sent to the independent data management group in the eVelos team. Quality control is going to be enforced by site visits and CRF review. The data will be handled, managed, and analyzed according to appropriate regional standard operating procedures. The study will be conducted in accordance with ICH-GCP and the Declaration of Helsinki.

## Discussion

Postoperative anemia occurs in around 18% of patients after oncologic gastrectomy
[16]. This signifies a considerable amount of patients in need of hemoglobin correction and prevention of chronic anemia. For gastric cancer patients high level evidence derived from prospective studies on anemia correction other than RBC transfusion are not available yet. Therefore we propose this prospective randomized placebo controlled trial.

Primary efficacy endpoint of this prospective study is the number of treatment responders after administration of either placebo or ferric carboxymaltose. Response is defined as an increase of the hemoglobin level of at least 2 g/dl related to the baseline hemoglobin 12 weeks after randomization. A hemoglobin level of 10 g/dl will be used as a cutoff value for our study based on the guidelines published by the American Society of Clinical Oncology and the American Society of Hematology for the treatment of cancer-related anemia, recommending Hb <10 g/dl as a treatment threshold
[20]. The increase of 2 g/dl was chosen on the basis of the former FERGIcor trial
[21], which defined treatment responders to ferric carboxymaltose when the hemoglobin level increased by 2 g/dl 12 weeks after initiation of treatment and revealed significant improvements in QoL.

After gastrectomy, damage on the gut may impact the ability of the patient to absorb iron from diet, limiting correction of iron deficiency anemia
[22]. Therefore an intravenous compound was chosen for this trial. To date, over 3,600 subjects were treated by ferric carboxymaltose in various clinical studies. Across those clinical studies
[14,15,21,23], replenishment of iron stores was consistently observed. In subjects with more severe or prolonged iron deficiency, anemia correction using ferric corboxymaltose consistently resulted in medically significant increases of Hb values. This improvement was usually found within 2 weeks. In addition to the correction of laboratory parameters, iron replacement therapy demonstrated significant improvements of QoL and functional status. In phase III studies, ferric carboxymaltose (Ferinject®) was reported to have improved tolerability and fewer side effects than iron sucrose
[24] together with faster correction of postoperative anemia.

Postoperative anemia may increase tumor resistance to possibly necessary adjuvant chemotherapy in advanced gastric cancer patients. It was found that anemia is the strongest prognostic factor for oncologic outcomes of 5-fluorouracil-based chemotherapy
[25]. Anemic patients revealed significantly lower response rates and overall survival rates than those with regular Hb-levels. Therefore it is of utmost interest to improve Hb-levels for postoperative AGC patients who are supposed to undergo adjuvant chemotherapy in a curative setting. Besides that, baseline Hb may be lower for advanced gastric cancer patients due to a higher risk of blood loss due to more invasive surgery (open procedure, more aggressive lymph node dissection, and longer operating time) compared to early gastric cancer patients. As the improvements on QoL may be more pronounced in this group, AGC patients will have to be stratified in a subgroup analysis.

Conclusively there is emerging evidence that patient blood management for postoperative isovolemic anemia may be superior to just observation or red blood cell transfusion. The proposed study represents a well powered randomized placebo-controlled trial in order to elucidate the influence of ferric carboxymaltose substitution on correction of isovolemic anemia and QoL in gastric cancer patients.

## Trial status

Recruiting. The first patient was randomized in January 2013.

## Abbreviations

AE: Adverse event; AGC: Advanced gastric cancer; ALT: Alanine aminotransferase; AST: Aspartate aminotransferase; CRP: C-reactive protein; EGC: Early gastric cancer; ESA: Erythropoiesis stimulating agent; FCM: Ferric carboxymaltose; FU: Fluorouracil; GGT: Gamma-glutamyl transpeptidase; Hb: Hemoglobin; HCG: Human chorionic gonadotropin; ID: Iron deficiency; IDA: Iron deficiency anemia; LDH: Lactate dehydrogenase; OS: Overall survival; PFS: Progression-free survival; QoL: Quality of life; SAE: Serious adverse event; SUSAR: Suspected unexpected serious adverse reaction; TSAT: Tranferrin saturation; TIBC: Total iron binding capacity.
